### Implementation parameters and outcomes

The RE-AIM framework will be used to evaluate the intervention and the implementation strategy. This framework is a practical way of evaluating health interventions and has previously been used in studies focused on changing individual behaviours [16]. Regarding patient implementation outcomes, the respondents’ satisfaction towards the PCC-consults will be assessed by elements of the validated ReproQ, which is based on the WHO-concept responsiveness and has been incorporated in our questionnaire [37, 38].

Healthcare providers’ implementation outcomes will be measured by a 23-item validated NoMAD (Normalisation MeAsure Development) questionnaire. The NoMAD questionnaire will be used to describe the health care providers’ views on how the intervention impacts their work and their expectations about whether the intervention could become a routine part of their work [39]. The healthcare providers will receive this questionnaire 3 months before the start of the intervention-phase and a follow-up questionnaire 6 months later. Barriers and facilitators regarding the implementation of the PCC-approach will be collected among healthcare providers and classified using the Flottorp et al. - checklist [40].

Finally, the feasibility of the implementation of the local care pathways will be evaluated among healthcare providers. We will measure to what degree the local care pathway was distributed amongst the healthcare providers and how healthcare providers experienced the convenience of this tool. In each municipality, focus groups with the local stakeholder coalition will be held 9 months after the start of the intervention and will be analysed using thematic analysis to identify key issues and themes. In these focus groups, information will be gathered on how the intervention complies with the heterogeneity of local settings, since differences in healthcare networks, logistics and practical issues call for tailored approaches.

### Sample size calculation

Based on the results from the APROPOS feasibility study, we anticipate on an odds ratio of 1.5 in lifestyle behaviour change during the preconception period (primary outcome). Based on the sample size estimation method of Hemming and Taljaard, with an alpha of 0.05, power of 80% and a low intraclass correlation Coefficient of 0.02, the sample size was calculated to be 363 participants per unit with 6 units (=municipalities; 2167 in total, 23 participants per month per municipality) [41]. Considering our inclusion criteria, almost all women who have their intake visit during the study period are eligible respondents. Based on previous experience, we expect that 50–60% of these women will fill out the questionnaire.

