**Methods:**

This study is an effectiveness-implementation hybrid type 2 trial. This involves a stepped-wedge cluster randomized controlled trial design aiming to include over 2000 future parents from six municipalities in the Netherlands. The intervention has a dual-track approach, focusing on both the uptake of PCC among future parents and the provision of PCC by healthcare providers. The PCC-approach consists of 1) a social marketing strategy directed towards prospective parent(s) and 2) a local care pathway to improve interdisciplinary collaboration. Data will be collected before and after the introduction of the intervention through questionnaires and medical records in each of the participating municipalities. The primary outcome of this study is change in lifestyle behaviours (e.g. folic acid use, smoking and alcohol use). Secondary outcomes are pregnancy outcomes (e.g. miscarriage, preterm birth, gestational diabetes) and the uptake of PCC. Moreover, a process evaluation will be performed, providing information on the efficacy, feasibility, barriers and facilitators regarding the implementation of the intervention.

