## Methods / design

### Study design

The APROPOS-II study uses a hybrid effectiveness-implementation design [14, 15]. In a stepped-wedge cluster-randomized controlled trial (RCT) we will implement and evaluate the effectiveness of the intervention. Randomization occurs at a cluster-level instead of an individual-level because the intervention has a community-approach in which the entire target population will be exposed to the intervention. All participating municipalities start with a control-phase, which will last 6–16 months depending on randomization order. The total duration of the study is 30 months (Fig. 1). The RE-AIM (reach, effectiveness, adoption, implementation, maintenance) framework will be used to evaluate the intervention and the implementation strategy [16].

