**Fig. 2 Fig2:**
[figure not shown]
Overview of the studypopulation of the APROPOS-II study. This figure shows how the number of people in the target population results in the total number of respondents for the APROPOS-II study. The intervention targets all men and women in their reproductive life span within a municipality. We aim to include 2267 women in the study

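### The printed recruitment totals disagree by about 5%, and 23 participants per month per municipality does not fit the per-municipality size together with control phases of up to 16 months

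*Protocol article*

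**What the plan says.** The size of the trial and its pace appear in four places in the protocol article.

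- Sample size calculation: "the sample size was calculated to be 363 participants per unit with 6 units (=municipalities; 2167 in total, 23 participants per month per municipality". The inputs given there are an odds ratio of 1.5, alpha 0.05, power 80% and an intraclass correlation of 0.02. The section treats nearly all women with an intake visit in the study period as eligible and expects 50–60% of them to complete the questionnaire.
- Fig. 2 legend: "We aim to include 2267 women in the study".
- Abstract, Methods: "aiming to include over 2000 future parents from six municipalities in the Netherlands", with data gathered both before and after the intervention is introduced in every municipality.
- Study design: "All participating municipalities start with a control-phase, which will last 6–16 months depending on randomization order", and "The total duration of the study is 30 months".

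**The concern.** The per-municipality size, the total and the monthly rate should follow from one another, and they do not. The gap between the totals is small. The gap between the rate and the timetable is not. The stated rate fills the stated size in roughly the time that the last municipality spends in its control phase.

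In a stepped-wedge trial the number of women is only part of the design. Power also depends on how those women are spread over calendar time, before and after each crossover. If the rate and the total imply different inclusion periods, the reader cannot tell which schedule the 80% refers to. Whoever runs recruitment cannot tell whether about 12 or about 23 respondents per municipality per month is on target.

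**Working it through.** **Totals**

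- 363 × 6 = 2178, which is 11 above the printed 2167 (0.5%). This is rounding-sized; 2167 / 6 = 361.2.
- 2267 − 2167 = 100, and 100 / 2167 = 4.6%. 2267 / 6 = 377.8 per municipality.

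**Rate against size**

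- Months to reach 363 in one municipality: 363 / 23 = 15.8.
- Months to reach the totals at 23 × 6 = 138 per month: 2167 / 138 = 15.7 and 2267 / 138 = 16.4.
- Women included in a 16-month control phase: 23 × 16 = 368, already more than 363. Against 377.8 (the Fig. 2 total), about 10 women would remain for the intervention phase.
- Inclusion over the whole 30-month study: 138 × 30 = 4140, which is 91% above 2167.
- Rate needed to spread the totals over 30 months: 2167 / 180 = 12.0 and 2267 / 180 = 12.6 per municipality per month.
- If 23 counted women approached: 4140 × 0.50 = 2070 and 4140 × 0.60 = 2484. This range spans every total, but the text calls the 23 participants.

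**Power**

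The documents give the odds ratio (1.5), the intraclass correlation (0.02), alpha and six clusters. My assumptions are a two-sided test, control proportions of 0.2–0.6 (none is printed), even inclusion, and the Hussey–Hughes variance:

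Var = I·s²·(s² + T·τ²) / [(I·U − W)·s² + (U² + I·T·U − T·W − I·V)·τ²]

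Here I is the number of clusters and T the number of periods. U, W and V are the sum of the treatment indicators, the sum of squared period totals and the sum of squared cluster totals. With m women per cluster-period, τ² = 0.02·σ², s² = 0.98·σ²/m and σ² = p̄(1 − p̄), where p̄ is the mean of the two proportions.

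I start with the layout that comes closest to the plan's own figure: a standard six-step design with seven equal periods and a control proportion of 0.5. An odds ratio of 1.5 gives 0.6, so p̄ = 0.55 and σ² = 0.2475.

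- m = 2167 / 42 = 51.6, s² = 0.00470, τ² = 0.00495.
- U = 21 and W = V = 91, so I·U − W = 35 and the second bracket is 441 + 882 − 637 − 546 = 140.
- Var = 6 × 0.00470 × (0.00470 + 7 × 0.00495) / (35 × 0.00470 + 140 × 0.00495) = 0.00129; the standard error is 0.0360.
- Power = Φ(0.1 / 0.0360 − 1.96) = 79%.

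This comes close to the stated 80%, but it is not a strict reproduction because the control proportion is assumed. In this layout 80% needs 2205 women.

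The same formula with crossovers assumed at 6, 8, 10, 12, 14 and 16 months and monthly periods gives the other rows.

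| Schedule | Women | Power, control proportion 0.2–0.6 |
|---|---|---|
| Standard six-step | 2167 | 66–79% |
| 6–16 month crossovers, inclusion over 30 months | 2167 | 46–59% |
| 6–16 month crossovers, inclusion ends at 16 months | 2167 | 63–77% |
| 6–16 month crossovers, inclusion over 30 months | 4140 | 72–85% |

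Replacing 2167 by 2267 raises power by less than 2 points throughout, for example from 79.4% to 81.0% in the six-step layout and from 58.9% to 60.8% over 30 months, both at a control proportion of 0.5.

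**The case against.** Much can be said for the plan.

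- Only two totals are printed. The figure of 2178 is a product that the article does not show, and its distance from 2167 is trivial. The 2267 may be a one-digit slip, or an aim set slightly above the calculated requirement. All this stands, and it makes the disagreement between totals minor.
- A reader might infer that recruitment runs for 30 months, so that 23 per month contradicts the total outright. The article gives 30 months as the study's duration, not as an inclusion window, and birth outcomes have to be collected after first-trimester enrolment. Over 16 months the rate gives 138 × 16 = 2208, close to every total. The timeline figure, which may show the window, is not available here. So 4140 is a consequence of one reading and not a planned number.
- A reader might also infer that a municipality closes at 363. No such rule is printed. A calculated size is normally a minimum, and the eligibility wording points away from a per-site stop.
- The scenario in which inclusion ends at 16 months is not the worst for power. At a control proportion of 0.5 it gives 77%, against 59% for the same total spread over 30 months. The power figures also rest on an assumed layout and control proportion.

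What survives does not need the 30 months or a cap. A window of about 16 months from a common start reconciles the rate with the total, but it leaves the last municipality with almost no women after crossover. A longer window at 23 respondents per month supplies those women and overshoots the total.

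**Conclusion.** The point holds in limited form. The printed targets differ by about 5%, with little effect on power. The stated rate, the stated size and control phases of up to 16 months do not fit together with data before and after the intervention in each municipality. That conclusion assumes continuous inclusion from a common start at 23 respondents per month. It would fall away if 23 means women approached, or if inclusion is not continuous.

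It would go too far to call the trial's size undefined, since a target of roughly 2170–2270 is clear. It would also go too far to say that the trial will lose its late intervention data or nearly double, because no stopping rule and no 30-month inclusion window is stated. Nor do the calculations show that the trial is underpowered. They show that the stated 80% depends on a schedule that the printed figures leave in conflict: under the assumptions above, 2167 women give anything from 46% to 79%.

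**What to change.** In the Sample size calculation section and the Fig. 2 legend:

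1. Print one total that equals the per-municipality number times six. If 2267 is a deliberate margin over the calculated requirement, say so.
2. Say whether 23 per month counts women approached or women responding.
3. Give the months of inclusion in each municipality before and after crossover, so that rate × months gives the total.
4. Restate the power for that schedule, with the control proportion that was assumed.

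The first three items cost one paragraph and one legend. The fourth needs a rerun of the existing calculation. If the restated power falls short of 80%, the sponsor would have to choose between revising the target or window and reporting the lower figure.

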### Statistical analysis

Statistical analysis will be performed using multilevel logistic regression analysis to take into account the clustering of respondents within municipalities. Data will be analysed anonymously on two levels; the respondents’ level (before and after the intervention) and the municipal level (differences between municipalities). Baseline characteristics will be compared between the pre- and post-intervention group and compared in a baseline table. Chi-square analysis and ANCOVA will be used to study the effects of the intervention on the adverse pregnancy outcomes. Adjusted odds ratios will be calculated taking into account the potential confounders: age, educational level and parity. *P*-values < 0.05 are considered statistically significant.

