### Aims and objectives

The aim of this study is to assess the effectiveness and the implementation process of a local PCC-approach (i.e. the intervention) on preconceptional lifestyle behaviours, health outcomes and the reach of PCC among prospective parents and healthcare providers. Therefore, we have specified the following objectives:
To determine the effect of the intervention on preconceptional lifestyle behaviours (e.g. smoking, alcohol use, folic acid use, physical activity) and other risk factors (e.g. body mass index, psychological distress, chronic illness) among women who recently conceived;to assess the effect of the intervention on the reach of prospective parents regarding PCC, the uptake of PCC and pregnancy preparation;to evaluate the implementation process in order to gain information on the feasibility, barriers and facilitators for the implementation of the local PCC-approach;to evaluate the sustainability of the intervention, with a specific focus on the diversity within and between the participating municipalities.

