### Implementation of the intervention

Concerning the uptake of PCC, the social marketing strategy has been developed by a professional and experienced marketing agency. A social marketing strategy uses commercial marketing technologies to design programs that can influence the behaviour of the target audience in order to improve personal welfare and that of society [18]. The theoretical foundation for this social marketing strategy is based on research regarding the target population’s perception from biological-, emotional-, social- and cultural point of views and resulted in the concept of “Woke Women®”, with the single-minded proposition: “Wake up smart (future) Mama! Let’s make your baby strong”. The social marketing strategy uses different channels of communication, e.g. online marketing, traditional offline marketing channels, word-of-mouth marketing and social networks will be addressed to start a social movement. Its purpose is to use existing social networks to encourage women to motivate each other towards healthy behaviour. Examples of materials used in the social marketing strategy are shown in Fig. 3 and more information about the social marketing strategy can be found on www.wokewomen.nl (in Dutch).

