### Clinical parameters and outcomes

Study parameters will be assessed by a questionnaire distributed among prospective parent(s) by the participating community midwifery practices in the first trimester of pregnancy. The questionnaire is based on validated questionnaires such as WHO - Quality of life questionnaire, the London Measure of Unplanned Pregnancy (LMUP), a validated preconception tool (www.zwangerwijzer.nl) and the APROPOS feasibility study [20, 21]. The questionnaire contains five sections: pregnancy planning, pregnancy preparation, healthy lifestyle behaviours and risk factors, personal situation and the prospective father. There are two versions of the questionnaire, one pre-implementation and one post-implementation. The post-implementation questionnaire contains additional evaluation questions about participant’s experiences with the social marketing strategy. An overview of all the variables in the questionnaire is shown in Table 1. The questionnaire is available in Dutch, English, Polish and Turkish; languages that are mastered by the majority of the inhabitants of the participating municipalities. The questionnaire for prospective fathers is shorter compared to the questionnaire for pregnant women and solely focusses on lifestyle behaviours and health beliefs.

**Table 1 Tab1:** Definition of primary and secondary outcomes of the APROPOS-II study

	Variable	Definition*
Pregnancy preparation	Level of pregnancy planning	London Measure of Unplanned Pregnancies (LMUP) [21]
	PCC health seeking behaviour	Acquired PCC-information through the internet, books, journals, folders or family & friends.
	PCC-consult	A consultation provided by a healthcare provider.
Modifying lifestyle behaviours & risk factors	Fruit intake	≥ 2 pieces of fruit a day [22]
	Vegetable intake	≥ 200 g of vegetables a day [22]
	Caffeine intake	≤ 1 caffeine-containing beverage [22]
	Exercising	≥ 150 min per week moderate or heavy intensive exercise, spread over various days [23]
	Smoking	No smoking [5, 24]
	Alcohol intake	No alcohol intake [5, 24]
	Folic acid usage	≥400 microgram per day, 4 weeks preconceptionally until 10 weeks gestation [5, 24]
	Medication usage	Risk-free medication [5]
	Psychological distress	A stable emotional state [5]
	Vaccination status	Vaccination status should be discussed with special attention to rubella, measles and whooping cough. Based on individual assessment of antibody titres; (re)vaccinations can be considered [24]

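### A single before/after indicator fits poorly with a campaign meant to build up; if calendar time is adjusted for, it can pull a real delayed effect close to null, so a supportive time-since-launch analysis should be prespecified

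*Protocol article*

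**What the plan says.** The model is given in the Statistical analysis section: "Statistical analysis will be performed using multilevel logistic regression analysis to take into account the clustering of respondents within municipalities". Data are to be analysed at the respondents' "level (before and after the intervention) and the municipal level (differences between municipalities"). The adjustment variables are also given: "Adjusted odds ratios will be calculated taking into account the potential confounders: age, educational level and parity". The section mentions no calendar-time term, no time-since-launch term and no transition period.

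Three other sections bear on whether an on/off contrast suits this intervention.

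- Implementation of the intervention describes an effect that spreads: "word-of-mouth marketing and social networks will be addressed to start a social movement", and "Its purpose is to use existing social networks to encourage women to motivate each other towards healthy behaviour".
- Clinical parameters and outcomes has the questionnaire handed out "by the participating community midwifery practices in the first trimester of pregnancy", while the primary outcome is lifestyle change made before conception.
- Study design staggers the launches after a control phase "which will last 6–16 months depending on randomization order", within 30 months in total.

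The fourth objective is to "evaluate the sustainability of the intervention", with attention to differences within and between municipalities.

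**The concern.** A before/after term treats the effect as complete from the day of launch. Two features of the protocol point the other way.

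The first is the mechanism. Word of mouth and a social movement take time.

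The second is the sampling window, which needs no assumption about build-up. A woman surveyed in her first trimester a few weeks after launch was already pregnant at launch. Her preconception behaviour cannot have been changed by the campaign, yet she counts as after.

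In a stepped-wedge model with calendar time, the on/off term draws much of its information from the months around each launch, when a delayed effect is smallest. Later growth is partly absorbed by the calendar-time terms. An intervention that works after some months could then be reported as having little effect, and the Discussion ties possible wider roll-out to this result.

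**Working it through.** **1. The plan's own figure.** The sample size is 363 per municipality for OR 1.5, alpha 0.05, power 80%, ICC 0.02 and 6 municipalities. The control rate is not given; I assume 0.5, so OR 1.5 gives 0.6. An individually randomised comparison needs 388 per group, 776 in all. The standard stepped-wedge design effect with 6 steps, one baseline period and n = 363/7 = 51.9 per cell is

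[1 + 0.02(7n − 1)] / [1 + 0.02(4n − 1)] × 3(0.98) / [2(6 − 1/6)] = (8.24 / 5.13) × 0.252 = 0.405.

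Then 776 × 7 × 0.405 ≈ 2199, within 1.5% of the stated 2167. Control rates of 0.4 to 0.5 reproduce it; 0.3 gives 2409 and 0.2 gives 3033. This design effect assumes calendar-time adjustment and a constant, immediate effect. Without time adjustment, power at the stated size would be about 95 to 99%. The planned size therefore suggests, but does not prove, that a time-adjusted model is intended.

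**2. Assumptions for the check.** Launches at months 6, 8, 10, 12, 14 and 16 (the article gives only the range 6 to 16); 30 months; 363 women per municipality spread evenly, m = 363/30 = 12.1 per month; ICC 0.02; control rate 0.5, plateau OR 1.5, so d = 0.10 and σ² = 0.55 × 0.45. The build-up curves c(s), with s the months since launch, are mine; the article gives none.

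**3. True mean effect while exposed.** Exposed municipality-months: 24 + 22 + 20 + 18 + 16 + 14 = 114. A linear 6-month build-up loses 3 months of full effect per municipality: (114 − 18)/114 = 0.84. A 12-month build-up loses 6: (114 − 36)/114 = 0.68. A pure 3-month lag loses 3: 0.84. A pure 2-month lag loses 2: (114 − 12)/114 = 0.89.

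**4. What the on/off term estimates.** Generalised least squares with V = (1 − ICC)σ²/m · I + ICC·σ² · J per municipality, Z = [on/off, month indicators] and y = d·c(s). The expected estimate is (ΣZ′V⁻¹Z)⁻¹ ΣZ′V⁻¹y, divided by d. ORs are exp(fraction × ln 1.5).

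| Effect curve | True mean (OR) | On/off, calendar time in (OR) | Power | On/off, no calendar time |
|---|---|---|---|---|
| Immediate | 1.00 (1.50) | 1.00 (1.50) | 59% | 1.00 |
| Linear, 6 months | 0.84 (1.41) | 0.36 (1.16) | 12% | 0.83 |
| Linear, 12 months | 0.68 (1.32) | 0.09 (1.04) | 4% | 0.67 |
| 2-month lag | 0.89 (1.43) | 0.48 (1.21) | 18% | 0.89 |
| 3-month lag | 0.84 (1.41) | 0.31 (1.13) | 10% | 0.83 |

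A logistic fit with fixed municipality effects gives nearly the same ORs (1.15, 1.03 and 1.12 to 1.13 for the 6-month, 12-month and 3-month-lag rows). The direction holds for ICC 0.001 to 0.05 and for a linear calendar trend. Short build-ups cost much less: 0.87 of the plateau for 1 month and 0.74 for 2 months.

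**5. Without calendar time.** The last column has no pull to null, provided there is no secular trend. But on this schedule the mean calendar month is 398/66 = 6.0 before launch and (2700 − 398)/114 = 20.2 after it. About 14 months of any drift would go into the estimate.

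**6. Alternatives under the 12-month build-up, calendar time included.**

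- Dropping the first 3 months after launch: 0.28 to 0.34 of the plateau (true 0.79 to 0.81), depending on whether exposure is counted at mid-month or month end.
- Two phases split at 6 months: average 0.37 (true 0.68), later phase 0.48 (true 0.88); standard error 0.057 against 0.046, a ratio of about 1.25.
- Term rising linearly to 12 months: 1.00 when the shape is right; standard error about 0.087, a ratio of 1.9. If the effect is in fact immediate it returns only 0.33.
- A separate effect for every 2-month exposure period: estimable and recovers its own average (0.75), but the standard error doubles and power is 13%.

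**The case against.** The strongest reply is that the attenuation belongs to a model the article does not state. As written, with no calendar-time term, the before/after estimate is within 0.01 of the true mean if there is no secular trend. That is correct, and the pull to null must be stated as conditional. It does not make the plan safe: without calendar time, drift enters the estimate; with it, a delayed effect is attenuated.

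A second reply is that the shape of the exposure term is usually left to an analysis plan, which is not shown. That is fair as to detail, and the phrase on levels of analysis does not exclude other exposure terms. What remains is that the only contrast the article states sits badly with its own mechanism and sampling window.

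Third, the size depends on assumed curves and launch dates. This stands for the 6- and 12-month build-ups. It applies less to the lag, which follows from first-trimester sampling; only its length is assumed.

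A reader might also infer that objective 4 cannot be answered. The documents do not support that. The objective stresses diversity within and between municipalities, and the maintenance element of RE-AIM, the provider questionnaire on whether the intervention could become routine, and the focus groups 9 months after the start all address it.

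Finally, the low powers are not all due to this point. On the assumed schedule an immediate effect already has only 59%, which is a separate sample-size matter.

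**Conclusion.** The point holds in a limited, conditional form. If calendar time is adjusted for, a single on/off indicator can recover as little as 0.09 to 0.48 of the plateau log OR under the delayed-effect curves of 2 to 12 months examined, where the true exposed mean is 0.68 to 0.89. Under the 12-month build-up an average OR of about 1.32 would appear as about 1.04. If calendar time is left out, there is no such attenuation, but secular trend is uncontrolled.

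A before/after term in either model cannot show whether the behavioural effect grows, persists or fades. That limits what the effect estimate adds to objective 4; it does not leave the objective without evidence.

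The figures rest on 2-month launch steps, even recruitment, a control rate of 0.5 and the assumed curves. It would be wrong to read them as showing that the trial will miss its effect.

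**What to change.** 1. Keep the before/after OR as the primary result.
2. Prespecify supportive models with municipality and calendar-time terms in which exposure is defined by time since launch: one with early months (for example the first 6) against later months, and one with an effect that rises gradually (for example linearly to 12 months).
3. Count women who conceived before their municipality's launch as unexposed, or as a separate transition group. Gestational age at the questionnaire and the launch date should allow this.
4. Report the later-phase and exposure-time-average estimates with intervals, and use them alongside the process evaluation for objective 4.
5. State that absence of effect will not be concluded from the constant-effect OR alone.

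This changes analysis wording only and should need no new data. The cost is precision: standard errors about 25% larger for the two-phase average and about 90% larger for the gradual-rise term. The plan should also say that the two-phase model removes only part of the attenuation, and that the gradual-rise term can be relied on only if its shape is right. For these reasons both models stay supportive.

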Secondary outcomes are pregnancy outcomes (e.g. miscarriage, preterm birth, gestational diabetes) and the uptake of PCC. The definitions of these pregnancy outcomes are given in Table 1 and will be collected from the participants’ medical records after obtaining additional informed consent. The uptake of PCC will be measured through a section in the questionnaire and by the records of the midwifery practices on PCC-consults.

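### Pregnancy outcomes are assigned chi-square and ANCOVA, which as named ignore municipality and calendar time in a stepped wedge, so these secondary tests may be invalid in either direction

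*Protocol article*

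**What the plan says.** The Study design section of the protocol article describes a stepped wedge: "In a stepped-wedge cluster-randomized controlled trial (RCT) we will implement and evaluate the effectiveness of the intervention". It adds that "Randomization occurs at a cluster-level instead of an individual-level" and that "All participating municipalities start with a control-phase, which will last 6–16 months depending on randomization order". Total duration is 30 months.

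The section on clinical parameters states: "Secondary outcomes are pregnancy outcomes (e.g. miscarriage, preterm birth, gestational diabetes) and the uptake of PCC". In Table 1, miscarriage, gestational diabetes, pregnancy-induced hypertension, pre-eclampsia, spontaneous preterm birth, referral, small for gestational age and congenital anomalies are yes/no outcomes. Mode of delivery has three categories, and APGAR is a score.

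The Statistical analysis section opens with a general statement: "Statistical analysis will be performed using multilevel logistic regression analysis to take into account the clustering of respondents within municipalities". It then names other methods for the clinical outcomes: "Chi-square analysis and ANCOVA will be used to study the effects of the intervention on the adverse pregnancy outcomes". The next sentence reads "Adjusted odds ratios will be calculated taking into account the potential confounders: age, educational level and parity", and the threshold is P "values < 0.05 are considered statistically significant". Calendar time, period or step is not mentioned anywhere in that section.

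**The concern.** A chi-square test of all intervention women against all control women treats the women as independent and the two groups as concurrent. Neither holds here. Women are clustered in six municipalities, and every municipality moves from control to intervention and never back, so the comparison is largely one of earlier with later. Any drift over the study in diagnosis, referral or obstetric practice is then credited to the intervention or set against it.

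ANCOVA as named does not repair this. It is a linear model for a continuous response, so it does not fit the binary and nominal outcomes and does not yield the odds ratios that the section promises.

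At stake is the evidence on clinical outcomes. The Discussion says trial data on maternal and perinatal outcomes are scarce and needed, and it links upscaling to better lifestyle that leads to better pregnancy outcomes. This is a stated choice of method, not a detail left to a fuller plan.

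**Working it through.** **The plan's own figure.** The protocol gives no sample size or power for the pregnancy outcomes, so there is nothing to reproduce for them. The stated total of 2167 is for the primary outcome. It is used below only as the largest number analysed.

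**Inputs from the protocol.** Six municipalities, control phase 6–16 months, 30 months in total, 2167 women, alpha 0.05, ICC 0.02 (sample size section, primary outcome).

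**Assumptions.** Crossovers at months 6, 8, 10, 12, 14 and 16; even recruitment over 30 months; two-sided tests; event rate 10%; ICC 0.001–0.02; trend 0–20% per year in the odds.

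**1. Calendar imbalance.**
- Control municipality-months: 6+8+10+12+14+16 = 66. Intervention: 180 − 66 = 114.
- The squared crossover months sum to 796. Mean control time = (796/2)/66 = 6.0 months.
- Mean intervention time = ((6×900 − 796)/2)/114 = 20.2 months.
- The gap is 14.16 months, or 1.18 years.
- A trend of 10% per year gives a spurious odds ratio of 1.10^1.18 = 1.12. A trend of 20% gives 1.20^1.18 = 1.24.
- Such a rise would exactly hide a true odds ratio of 1/1.12 = 0.89 or 1/1.24 = 0.81.

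**2. Clustering alone.** Let R be the true variance of the pooled difference divided by the variance that chi-square assumes.
- R = (1 − ρ) + ρ·S/V, with S = Σ(w1 − w0)² and V = 1/N1 + 1/N0. Here w1 = (30 − c)/114 and w0 = c/66 for crossover month c.
- The differences w1 − w0 are ±0.1196, ±0.0718 and ±0.0239, so S = 0.0401.
- N1 = 2167×114/180 = 1372 and N0 = 2167×66/180 = 795, so V = 0.00199 and S/V = 20.16.
- Type I error = 2[1 − Φ(1.96/√R)].

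| ICC | R | Type I error |
|---|---|---|
| 0.001 | 1.02 | 5.2% |
| 0.005 | 1.10 | 6.1% |
| 0.01 | 1.19 | 7.3% |
| 0.02 | 1.38 | 9.6% |

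At ICC 0.02 the figure depends on the schedule: 13.0% if recruitment stops at month 22, and 23.3% for a standard seven-period wedge.

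**3. Clustering plus trend, no intervention effect.**
- The shift of the test statistic is δ = ln(1+g) × 1.18 × √(p(1−p)/V), where g is the yearly rise in the odds.
- With p = 0.10 the last factor is √(0.09/0.00199) ≈ 6.73. Then δ = 0.757 for g = 10% and 1.448 for g = 20%.
- Rejection = 1 − Φ((1.96 − δ)/√R) + Φ((−1.96 − δ)/√R). For ICC 0.005–0.02 this gives 13–16% (g = 10%) and 31–33% (g = 20%).
- Simulation of null trials agrees: about 12–16% and 31–32%.

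**4. Direction.** In simulations on the 6–16 month schedule (10% events, ICC 0.02) with a trend odds ratio of 1.5 over the study, chi-square rejected in 26.7% of runs. In 26.5% it pointed to more events under intervention. With a trend of 0.67 it rejected in 28.8%, and in only 0.8% did it point to more events.

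**5. After adjustment.** Logistic regression with fixed municipality and period effects gave type I error of 3.3–6.7% in every scenario (600 runs each; Monte Carlo standard error √(0.05×0.95/600) = 0.9 points).

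**The case against.** Several points on the other side stand.

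- A reader might infer that chi-square is wrong for binary data. It is not: it suits binary and nominal outcomes when observations are independent. The data-type objection applies to ANCOVA only, and ANCOVA could serve the APGAR score.
- A reader might infer that p-values will certainly be too small. Each municipality contributes both conditions, so much of the between-municipality variance cancels. No ICC is given for pregnancy outcomes, and at 0.001–0.005 clustering alone adds only 0.2–1.1 points.
- A reader might infer that the multilevel model is reserved for the primary outcome. The opening sentence does not say so. Chi-square could be the crude step, with adjusted odds ratios from the multilevel model to follow. The section does not settle this, and even on that reading the listed covariates are age, education and parity, without calendar time.
- Pregnancy outcomes need additional consent, so fewer women may be analysed. With half of them (an assumption), ICC 0.01 and 10% events, rejection falls to about 6%, 9% and 17–19% for trends of 0, 10 and 20% per year. With 5% events, all women, ICC 0.005 and a 5% yearly trend it is about 7%.
- Nothing in the documents supports a 20% yearly trend. Even recruitment is also assumed: at 23 per month, 363 women are reached in 363/23 ≈ 16 months.

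These points limit the size of the problem. They do not make the named tests fit the design.

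**Conclusion.** The concern holds in a limited form. The methods named for the intervention effect on pregnancy outcomes do not account for municipality or calendar time, so those secondary tests may be invalid. Calendar-time bias is the larger part and can run either way. Clustering is the smaller part on the 6–16 month schedule. The 12–32% range is illustrative, because it rests on assumed event rates, ICCs, trends, crossover months and recruitment pattern.

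A reader might go further and conclude that the primary result or the upscaling decision is compromised. The documents do not support that. The sentence concerns secondary outcomes without stated power, and upscaling is tied first to improved lifestyle behaviour. Severity is therefore moderate.

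**What to change.** Replace the chi-square and ANCOVA sentence with the following plan.

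- Binary pregnancy outcomes: multilevel logistic regression with municipality effects and calendar period as a fixed effect, adjusted for age, educational level and parity, with a small-sample correction for six clusters. Write out the period term. It cannot be taken over by reference, because the section states none for any model.
- Rare outcomes: a reduced period structure, fixed in advance.
- Mode of delivery: a matching multinomial model, or prespecified binary contrasts.
- APGAR: a suitable mixed model with the same period and municipality terms.
- Chi-square: descriptive tables only.

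The cost is analysis wording, somewhat more analysis work and wider intervals. No new data are needed.
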